Recently, the brain–gut axis, serving as a bridge between the central nervous system (CNS) and the GI tract [8, 9], has been proved to be one of the possible mechanisms of acupuncture improving GI. Through the brain–gut axis, signals from the brain affect the sensory, motor, and endocrine modalities, as well as the microflora of the GI gut. Similarly, visceral information from the microbiota may also influence brain functions [8]. In our previous studies, our research group also found that electroacupuncture stimulation of Zusanli (ST36) could lead to imaging changes in different brain regions observed by functional magnetic resonance imaging (fMRI) [10]. These results demonstrated that acupuncture may act through the brain–gut axis. Brain–gut peptides are distributed along the GI tract and in the CNS and are involved in the modulation of GI tract processing [11]. The secretion of substance P (SP) and vasoactive intestinal polypeptide (VIP) are decreased, motilin and cholecystokinin (CCK) are increased after treatment with electrical acupuncture (EA) in rats with irritable bowel syndrome (IBS) [12, 13]. However, until now, most research on this mechanism has focused on animal studies and the treatment effect of acupuncture or transcutaneous electrical acupuncture stimulation (TEAS) on patients after abdominal surgery—whether the prevention effect of TEAS on PGD through brain–gut peptides or not—is still unclear.

Based on previous studies, our aim is to confirm the preventive effect of TEAS on PGD in patients undergoing abdominal surgery. Changes in the perioperative brain–gut peptides may prove that the regulation of GI function by TEAS stimulation plays a role through the brain–intestinal axis. Health economic indicators (length of stay, cost of hospitalization, etc.), will also demonstrate the significance of perioperative TEAS stimulation on postoperative GI function recovery of patients undergoing abdominal surgery. This study will provide further evidence as to whether TEAS should be included in enhanced recovery after surgery (ERAS) protocols for patients undergoing GI surgery.

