### Outcome assessment

A blind observer from the Data Monitoring Committee (DMC) will collect all outcome data after surgery. The primary outcome of this study will be time to the first bowel motion by auscultation. The same surgical residents will listen to the bowel sounds every 4 h postoperatively. Time to first bowel motion is the duration until regular bowel sounds (more than two sounds every minute) are first heard after surgery [14].

The secondary endpoints will include the time to first flatus and time to defecation. This information will be obtained from participant questionnaires filled out once daily with the help of nurse staff. To observe changes in plasma brain–gut peptides, such as 5-HT, SP, VIP, gastrin, and CCK, we will collect venous blood from patients before the operation and on the first and third days after the operation. We will then centrifuge and freeze the plasma supernatant for later testing. We cooperate with our clinical experimental center to collect, code, centrifuge, freeze store, store, and test blood samples by a professional team. Secondary endpoints will also include VAS score of postoperative pain, vomiting and nausea, length of stay in the ICU, length and cost of stay in the hospital, as well as clinical complications such as fever, pneumonia, wound infection, and bleeding. Secondary outcome will be assessed by the medical team. The length of hospital stay is calculated as the number of days from the date of the operation to the date of discharge. Criteria for hospital discharge will include stable vital signs, the ability to tolerate solid foods after defecation without nausea or vomiting, and the occurrence of no other complications after the operation.

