### Statistical methods

Statisticians are responsible for negotiating with major researchers to develop statistical analysis plans, establish databases, and conduct statistics with the SPSS statistical analysis system. All data will be collated by statisticians. The intention processing principle in SPSS 22.0 will be used for the data analysis. A unilateral test will be used for statistical results, and a *P* value < 0.05 will be considered statistically significant. The results will be expressed as the mean ± standard deviation. The t-test will be used for the normality and homogeneity of data, the hypothesis test of superiority will be used for major outcome indicators, the chi-square test will be used for normal distribution data, and the rank sum test or Fisher’s exact probability method will be used for non-normal distribution data. Statistical methods for the main efficacy indicators have been determined by the Capital Medical University statistical department.

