In recent years, research on the brain–gut axis has become a hot topic. The brain affects the sensation, movement, endocrine, and microflora of the GI tract through the brain–gut axis. Gut information from the microbiome may also affect brain function [8, 9, 23]. Brain–gut peptide, regulation of the vagus nerve, and nerve excitability of the posterior horn of the spinal cord are all possible mechanisms of the brain–gut axis regulating GI function [24]. Brain–gut interaction is achieved by a variety of substances in the endocrine cells of the CNS, neuroendocrine system, and GI tract, which act as neurotransmitters and hormones at the same time and are called brain–gut peptides [25]. Brain–gut peptides widely regulate GI activity and are therefore closely associated with PGD. Major excitatory neurotransmitters include histamine, 5-HT, SP, calcitonin gene-related peptide (CGRP), and adrenocorticotropin releasing factor-related peptide (CRF). Major inhibitory neurotransmitters include cholecystokinin (CCK), nitric oxide (NO), norepinephrine (NE), and VIP [26]. Clinical studies have confirmed that the contents of 5-HT in the intestinal mucosa of patients with GI dysfunction are significantly increased. Other studies have found that EA can regulate the secretion of SP, SP receptor, and VIP in the IBS model colon [27]. CRF can induce repeated defecation in rats. Both sets of findings have confirmed the possible role of brain–gut peptides in patients with GI dysfunction [28].

Although the clinical therapeutic effect of electroacupuncture on GI dysfunction has been confirmed by many investigations, the role of preventive acupuncture treatment of perioperative patients, especially high-risk patients (receiving abdominal surgery), and the mechanism of this role associated with the brain–intestinal tract have not been confirmed by any clinical studies and still need to be verified by much research.

However, some limitations in this study should be noted. First, the main outcome measures are subjective evaluation scales that lack objective evidence to directly support the effect of a given treatment. Second, how to ensure the timely and accurate postoperative follow-up is very important and difficult in this study. We have established guidelines and training for research staff. Patient self reporting is another supplement.

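### The blanket one-sided rule at P < 0.05 covers the brain–gut peptides, for which no direction is declared and the background points both ways; the mechanism wording also goes beyond what the comparison can show

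*Protocol article*

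**What the plan says.** Outcome assessment lists the peptides among the secondary endpoints: "To observe changes in plasma brain–gut peptides, such as 5-HT, SP, VIP, gastrin, and CCK". The list is introduced as examples, so five is a minimum. On sampling, the same sentence continues: "we will collect venous blood from patients before the operation and on the first and third days after the operation".

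Statistical methods sets one rule for the whole trial: "A unilateral test will be used for statistical results", with a P "value < 0.05 will be considered statistically significant". No endpoint is excepted. For continuous data it names the t-test ("The t-test will be used for the normality and homogeneity of data") and, for non-normal data, the rank sum test. Neither takes a covariate.

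On interpretation, the Introduction says: "Changes in the perioperative brain–gut peptides may prove that the regulation of GI function by TEAS stimulation plays a role through the brain–intestinal axis". The closing paragraph of the Discussion goes further and expects the trial to show the mechanism of TEAS. The Abstract is more cautious in both places where it touches on mechanism.

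**The concern.** A one-sided test needs a direction fixed before the data are seen. For the primary outcome that direction is clear, since earlier recovery is better. For a plasma peptide it is not, and the article declares none.

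Where the rule says one-sided but the direction is open, the natural reading at analysis is to test on the side to which the data point. That doubles the nominal error rate of each test. The reverse problem also exists: if a direction is fixed and turns out wrong, a real change the other way cannot be declared.

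The peptides carry one of the two stated purposes of the trial, the brain–gut mechanism. A chance finding on one of them could therefore be reported as evidence of mechanism. Even a true between-arm difference would show only that TEAS alters a peptide, not that the peptide carries the effect on GI recovery.

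**Working it through.** **Step 1. Is a direction available in the document?** The article gives no figure for the peptides to reproduce, so this step compares text. The Introduction reports changes after electroacupuncture in rats with irritable bowel syndrome. The Discussion gives excitatory or inhibitory roles; for CCK it says "Major inhibitory neurotransmitters include cholecystokinin (CCK", with VIP in the same list.

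| Peptide | Change after electroacupuncture (Introduction) | Role (Discussion) | Consistent with better motility? |
|---|---|---|---|
| SP | down | excitatory | no |
| CCK | up | inhibitory | no |
| VIP | down | inhibitory | yes |
| 5-HT | none given | excitatory, yet raised in the mucosa of patients with GI dysfunction | unclear |
| Gastrin | none given | none given | no direction |

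Only VIP has a coherent direction.

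**Step 2. Level per test.** A one-sided test at 0.05 rejects when Z > 1.645. If the side is chosen after seeing the data, it rejects when |Z| > 1.645, which has null probability 2 × 0.05 = 0.10.

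**Step 3. Number of tests.** 5 named peptides × 2 postoperative days = 10 between-arm comparisons, if each is tested separately.

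**Step 4. Chance of at least one false positive, independent tests.**
- Direction fixed in advance: 1 − 0.95^10 = 0.401.
- Direction chosen from the data: 1 − 0.90^10 = 0.651.
- With five tests only: 1 − 0.95^5 = 0.226 and 1 − 0.90^5 = 0.410.

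**Step 5. Correlated tests.** The document gives no correlations, so these are assumptions: between days 0 to 0.8, between peptides 0 to 0.5. Ten null normal statistics were simulated with 400,000 draws per setting. Selected settings, including both extremes:

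| Between days | Between peptides | One-sided 0.05, direction fixed | One-sided 0.05, direction chosen | Two-sided 0.05 |
|---|---|---|---|---|
| 0 | 0 | 40.2% | 65.1% | 40.2% |
| 0.5 | 0.3 | 31.4% | 58.2% | 35.3% |
| 0.8 | 0.5 | 23.5% | 46.2% | 27.2% |

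Two-sided testing at 0.05 removes the doubling caused by the open direction. It does not remove the multiplicity of ten tests. At 0.005 per test (0.05/10), the two-sided figure falls to 3.7% to 4.9% over the same settings.

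**Step 6. Precision from the preoperative sample (separate from error rates).** With baseline–outcome correlation r (assumed), the relative variance of the treatment comparison is 1 for post-values, 2(1 − r) for change scores and 1 − r² for ANCOVA.

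| r | Post-value | Change | ANCOVA | ANCOVA cut against post-value | ANCOVA cut against change |
|---|---|---|---|---|---|
| 0.3 | 1 | 1.4 | 0.91 | 9% | 35% |
| 0.5 | 1 | 1.0 | 0.75 | 25% | 25% |
| 0.7 | 1 | 0.6 | 0.51 | 49% | 15% |

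**The case against.** The best defence is that this is a condensed article and that an analysis plan is to be developed by the statisticians with the researchers. Covariates and multiplicity rules for secondary biomarkers commonly sit there. That stands: silence on either is not a fault. The aim of observing changes also implies some use of the preoperative sample.

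The direction argument can be challenged too. Results in rats with irritable bowel syndrome and general transmitter roles are not predictions for plasma levels after surgery in these patients. That is fair, but it strengthens the point: if neither source predicts a direction, the article has none on which to base a one-sided test.

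A reader might infer that a false proof of mechanism is likely under this plan. The document does not support that. With directions fixed in advance the chance is about 24% to 40%, below one half. The higher range needs the direction to be chosen from the data. Both ranges need ten separate tests and a rule that any one positive counts, and the article states no such rule.

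A reader might also infer that leaving out the preoperative value adds to the false positives. It does not: in a randomized comparison the omission costs precision and leaves the type I error unchanged.

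Finally, much of the mechanism wording is hedged. The Abstract is cautious, and the Introduction sentence contains a 'may'. Only the end of the Discussion is unguarded.

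**Conclusion.** The concern holds as a point about sidedness and wording for a secondary aim. The one-sided rule at 0.05 is stated without exception, so it is a wrong rule for the peptides and not a gap left to the analysis plan. No direction is declared. The background is inconsistent for SP and CCK, coherent for VIP, and silent for gastrin.

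If directions are chosen after the fact, the level per test is 0.10, and the chance of at least one false positive in ten is 65% if independent and about 46% to 65% over the assumed correlations. This rests on ten separate tests and on any one positive being read as support; both are assumptions.

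The precision lost by the named tests is a separate and lesser matter. The mechanism claim is too strong whatever the test results, because the planned comparison does not identify mediation.

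**What to change.** - In Statistical methods, except the peptides from the one-sided rule and test them two-sided at 0.05. The critical value rises from 1.645 to 1.960, so individual results become slightly harder to declare significant.
- As a separate gain in precision, analyse each postoperative value (log scale if skewed) by ANCOVA or a repeated-measures model, with the preoperative value and the stratification factor, type of surgery, as covariates, in place of the t-test or rank sum test.
- Label the peptide results exploratory. A multiplicity adjustment such as Holm is optional and may be placed in the analysis plan.
- In the Introduction and the closing paragraph of the Discussion, replace the claims that the peptides may prove, or that the trial will show, the mechanism with wording such as: to explore whether TEAS changes brain–gut peptides.

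The cost is wording and analysis code only. The samples are already planned, the plasma is frozen for later testing, and 106 of 280 participants had been recruited when the article was written. The change should be fixed before the peptide results are examined.

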### Sample size calculation

Due to a lack of related reports on the preventive usage of TEAS in patients undergoing GI surgery, we evaluated the effectiveness of TEAS according to our pre-experimental results. A priority-effectiveness test was used and the ratio between the groups was 1:1. According to the pre-experimental results, a difference in time to first bowel sounds of 12 h was thought to be clinically significant and selected as the effect size. This result in a hazard ration of 1.5. The COX regression sample size calculation formula was used to complete the sample size estimation. We set unilateral α = 0.05 and power = 0.90; PASS 2011 software was used for sample estimation and a total of 256 effective cases were estimated. According to the above sample estimation result and assuming 10% patient loss, a minimum of 280 cases is required. Therefore, we have set the required number of cases in this study to 280 cases, including 140 cases in the TEAS group and 140 cases in the sham TEAS group. Our General Surgery Department performs 400–500 cases of GI surgery per year; consequently, this study period is set at 2 years.

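### The stated 256 cases match a two-sided α of 0.05, not the one-sided 0.05 that the protocol names for sizing and then uses for testing

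*Protocol article*

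**What the plan says.** All references are to the protocol article. Under *Sample size calculation*, a 12-hour difference in time to first bowel sounds is translated into an effect size: "This result in a hazard ration of 1.5". The method is given as "The COX regression sample size calculation formula was used to complete the sample size estimation", with equal allocation. The error rates and software are given as "We set unilateral α = 0.05 and power = 0.90; PASS 2011 software was used for sample estimation", and the result is that "a total of 256 effective cases were estimated". The loss allowance is added afterwards: "assuming 10% patient loss, a minimum of 280 cases is required". No event probability, censoring rate or covariate R-squared is stated.

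Under *Statistical methods*, the same sidedness and level become the decision rule: "A unilateral test will be used for statistical results, and a *P* value < 0.05 will be considered statistically significant". *Trial design* describes a superiority analysis.

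**The concern.** A sample size statement should let a reader recover the number from its inputs. Here the hazard ratio, allocation, power and formula are all given, yet the stated α leads to a number well below 256, while a different α leads to 256 exactly. This suggests that the number was worked out for one significance level and the trial will be judged at another, easier one.

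What is at stake is the strength of evidence needed to claim benefit on the primary outcome. Moving from one-sided 0.025 to one-sided 0.05 doubles the chance of declaring TEAS effective when it is not. The article offers no reason for the looser level. A superiority aim does not supply one, because superiority can be tested at either level.

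**Working it through.** **Inputs, all from *Sample size calculation*:** hazard ratio 1.5; 1:1 allocation; power 0.90 (z = 1.2816); α = 0.05, one-sided; stated result 256; loss 10%; final number 280.

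**Formula.** For a binary 1:1 covariate in a Cox model (Schoenfeld), the required number of events is

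D = (z_α + z_β)² / (0.25 × (ln HR)²).

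With ln 1.5 = 0.4055, the denominator is 0.25 × 0.1644 = 0.0411. If every patient has the event, D is also the number of patients.

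**Step 1: reproduce 256.**

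| α setting | z_α | (z_α + z_β)² | D | Rounded up |
|---|---|---|---|---|
| One-sided 0.05 (as stated) | 1.6449 | 8.564 | 208.4 | 209 |
| Two-sided 0.05 (= one-sided 0.025) | 1.9600 | 10.507 | 255.65 | 256 |

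The stated setting misses by 47 cases (47/209 = 22%), too much for rounding. The two-sided setting matches exactly.

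**Step 2: other variants.** Freedman's formula gives 215 at one-sided 0.05 and 263 at two-sided 0.05. At 80% power the Schoenfeld figures are 151 and 191. No one-sided 0.05 variant on the stated inputs comes near 256.

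**Step 3: power with 256 events.** Power = Φ(ln HR × √D / 2 − z_α), and 0.4055 × 16 / 2 = 3.244.

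- One-sided 0.05: Φ(3.244 − 1.645) = 94.5%.
- Two-sided 0.05: Φ(3.244 − 1.960) = 90.0%.

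**Step 4: the hurdle.** The chance of a false claim of benefit is 5% at critical z 1.645 and 2.5% at critical z 1.960. Within the sizing model, the standard error of the log hazard ratio is 2/√256 = 0.125. The smallest observed hazard ratio called significant is then exp(1.645 × 0.125) = 1.23, against exp(1.960 × 0.125) = 1.28. These two ratios only illustrate the sizing model, since *Statistical methods* does not name a Cox analysis.

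**Step 5: loss.** 256/0.9 = 284.4, so 285 patients are needed for 256 to remain after 10% loss. Even 256 × 1.1 = 281.6 exceeds 280. With 280 patients, 10% loss leaves 252. If all 252 have the event, power at two-sided 0.05 is Φ(3.218 − 1.960) = 89.6%. Put the other way, (280 − 256)/280 = 8.6% loss is covered.

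**The case against.** The best reply is that 256 is a count of cases, not events, and that PASS can take an event rate which a condensed article may have left out. At one-sided 0.05, 256 patients would be right if the overall event probability were 208.4/256 = 0.81. Such a value can be constructed. If times were exponential with medians 12 hours apart and hazard ratio 1.5, the medians would be 36 and 24 hours. Over 72 hours, 75% and 87.5% would reach the event, 81.25% on average, and 208.4/0.8125 = 256.4. Over 96 hours the figure falls to 234.1.

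This part stands: a reader might infer that 256 can only have come from a two-sided calculation, and the article does not prove that. But it states no medians, observation limit or event rate, and it adds loss separately. Two-sided 0.05 gives the number exactly without any unstated input, so it is the simpler explanation.

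It is also fair to say that the two sections agree with each other on sidedness, that the 5% one-sided level is openly stated, and that nothing in the article promises 2.5%. The mismatch is between the stated level and the stated number, not between the two sections.

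**Conclusion.** The point holds on the inputs the article gives: one-sided 0.05 needs 209 events, and the reported 256 is the two-sided 0.05 figure. The analysis rule then uses one-sided 0.05, with twice the false-positive risk for benefit of the level that reproduces 256. This rests on the Schoenfeld form of the Cox formula and on every counted case having the event.

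Three stronger readings should not be drawn:

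- **That the trial is underpowered, or that α, power and number cannot all hold.** With 256 events at one-sided 0.05, power is 94.5%, so at least 90% is met. What fails is 256 as the number required.
- **That one-sided testing prevents complications from showing harm.** *Statistical methods* makes a general statement about sidedness and gives no direction for complications, so that conclusion supplies a direction the text does not contain.
- **That the loss slip matters in itself.** It costs about 0.4 percentage points of power at two-sided 0.05 (90.0% to 89.6%).

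**What to change.** **Preferred.** In *Sample size calculation* and *Statistical methods*, replace the one-sided 0.05 level with two-sided α = 0.05 (or, equivalently for a claim of benefit, one-sided 0.025), and report two-sided 95% confidence intervals. Keep 280 patients. State that the 256 assumes every counted patient has the event, if that is what was entered.

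**Alternative, if one-sided 0.05 was intended.** Either correct the requirement to about 209 events, or state the event rate entered in PASS (about 0.81) that gives 256. In both cases justify the level. The PASS inputs should be checked before choosing, because the two repairs rest on different event assumptions.

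**Loss.** State that 280 covers 8.6% loss, or that 10% loss leaves 252 and about 89.6% power at two-sided 0.05 if all have the event.

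**Cost.** The preferred change adds no patients. It makes the success hurdle stricter, which is a small downside but a real change to the decision rule. *Trial status* reports 106 participants recruited and the trial ongoing, so it should be recorded as a dated amendment made before the outcome data are analysed. If an event rate near 0.81 did apply, 256 patients would yield about 208 events, and power at two-sided 0.05 would be Φ(0.4055 × √208 / 2 − 1.960) = Φ(0.964), or about 83%.

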### Randomization and blinding

This is a single-blinded study. The doctors from the traditional Chinese department who will conduct the TEAS stimulation and the anesthesiologists will know the grouping information and participants. The observers of major outcomes after surgery will be blinded. Randomization will be conducted by a computer-generated blocked randomization list with 70 blocks of four patients per block. The participants will be consecutively randomly assigned to the TEAS group or the sham group at a ratio of 1:1. Allocation shall proceed via duplicate, sealed, numbered envelopes, which will be stored by the clinical trial quality control inspectors and the main person in charge of this research group. The blind bottom shall not be opened without reason during the trial. The outcome assessors and the statisticians will not participate in the treatment, they will perform the outcome evaluation and the statistical analysis independently.

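### 280 patients is not the minimum for 256 effective cases at 10% loss: it absorbs 8.6% (24 patients), and the sentence should say so

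*Protocol article*

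**What the plan says.** All the figures stand in the protocol article, mostly under Sample size calculation.

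- Error rates: "We set unilateral α = 0.05 and power = 0.90". Statistical methods agrees on the side of the test: "A unilateral test will be used for statistical results".
- Effect: "This result in a hazard ration of 1.5", derived from a 12 h difference in time to first bowel sounds, with equal allocation ("the ratio between the groups was 1:1").
- Method and result: "The COX regression sample size calculation formula was used to complete the sample size estimation", and "a total of 256 effective cases were estimated".
- Inflation for loss: "According to the above sample estimation result and assuming 10% patient loss, a minimum of 280 cases is required".

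The total of 280 is then split into 140 per arm. It is also the recruitment figure under Study participants and recruitment, and the length of the list under Randomization and blinding ("70 blocks of four patients per block", and 70 × 4 = 280). No event rate or censoring proportion is given.

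**The concern.** A requirement (256), a loss allowance (10%) and a total (280) are stated together, and the total is called a minimum. Any two of them fix the third, and these three disagree. A number described as a minimum should at least meet the requirement it was built from, and this one falls short by a few patients.

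What is at stake is mainly the accuracy of a stated design figure. The arms, the recruitment target and the randomization list all rest on 280, and a reader will take it that the trial can lose one patient in ten and still hold its 256 effective cases. It cannot. Trial status names an imprecise sample size calculation among the reasons for the current, third version, so this section has already been revised once and the mismatch remains.

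**Working it through.** **Inputs.** From Sample size calculation: 256 effective cases, 10% loss, total 280, one-sided α = 0.05, power 0.90, hazard ratio 1.5, allocation 1:1. From Randomization and blinding: blocks of four. The event rate is not stated and is treated below as an assumption.

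**Step 1: can 280 be reproduced from 256 and 10%?**

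- Correct inflation, n/(1 − loss): 256/0.90 = 284.4, so 285. Equal arms need 286, and whole blocks of four need 288.
- Common short cut, n × (1 + loss): 256 × 1.10 = 281.6, so 282.

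Neither gives 280. It lies 5 patients (5/285 = 1.8%) below the correct figure and 2 below the short cut.

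**Step 2: what does 280 deliver?**

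- At 10% loss: 280 × 0.90 = 252, which is 256 − 252 = 4 short.
- Losses it can absorb while keeping 256: 280 − 256 = 24, and 24/280 = 8.6%. A 10% loss would be 28 patients.

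**Step 3: where does 256 come from?** The Schoenfeld formula for a Cox comparison with 1:1 allocation is

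events = (z_α + z_β)² / (0.25 × (ln HR)²), with ln 1.5 = 0.4055.

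- Two-sided 0.05: (1.960 + 1.282)² / (0.25 × 0.1644) gives 256, the plan's figure.
- One-sided 0.05, as stated: (1.645 + 1.282)² / (0.25 × 0.1644) = 208.4, so 209 events.

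There are thus two ways to reach 256: a two-sided test with an event in every patient, or the stated one-sided test with an event rate of 208.4/256 = 0.81. The protocol does not say which was used.

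**Step 4: what does the gap do to power?** Power = Φ(ln 1.5 × √events / 2 − z_α).

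| Basis | Events from 252 retained patients | Power |
|---|---|---|
| One-sided 0.05 (stated), event in every patient | 252 | 94.2% |
| One-sided 0.05 (stated), event rate assumed 0.81 | about 205 | 89.6% |
| Two-sided 0.05 (not stated), event in every patient | 252 | 89.6% |

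The last two rows agree because each is a basis on which 256 patients give about 90%. On the first row, 209 events suffice; 209/0.90 = 232.2, so 233 patients would cover a 10% loss and 280 is ample.

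**The case against.** The best defence is that this is rounding. The gap is 5 patients in 285, and 280 is the multiple of four nearest to 281.6, which would suit a list made of blocks of four. That is an inference, since the article does not explain the rounding. It also does not rescue the sentence: rounding down cannot yield a minimum, and 281.6 is itself the less accurate inflation. What stands is the argument about weight. No design, analysis or recruitment decision turns on four effective cases.

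A second defence is that 256 may overstate the requirement. On the stated one-sided inputs with an event in every patient, 209 events are enough. That is a fair reason not to turn the mismatch into a claim about power. It does not make 256, 10% and 280 consistent, because the protocol itself declares 256 as the number needed.

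A reader might go further and infer that the trial is underpowered, with 89.6% in place of 90%. The documents do not support this. The 89.6% requires either a two-sided test, which the protocol does not state, or an event rate near 0.81, which it does not give. Nor do they support the inference that more patients must be recruited.

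**Conclusion.** The point holds as an arithmetic inconsistency of low severity. Given 256 effective cases and 10% loss, 280 is not the minimum; 285 is. At 10% loss 280 leaves 252, and it keeps 256 only up to 24 losses (8.6%). This part rests on the protocol's own three figures and on no further assumption.

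A shortfall against 90% power is not established. With 252 retained patients at one-sided 0.05 and hazard ratio 1.5, power runs from about 89.6% to 94.2% as the assumed event rate runs from about 0.81 to 1. The lower end is the rate at which 256 patients would give exactly 90% on the stated inputs. At a lower rate 256 itself would be too few, which is a different question. Which side of the test and which event rate lie behind 256 is a separate and larger matter (256 against 209), and correcting the loss allowance does not settle it.

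**What to change.** Keep 280, delete the word *minimum*, and replace the inflation sentence with one that adds up. For example: 280 patients (140 per arm) will be randomized, which allows for a loss of 8.6% (24 patients) with 256 effective cases remaining.

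Do not add a power figure to that sentence unless its sidedness and event rate are given with it. In particular, 89.6% calculated two-sided would contradict the one-sided α in the same paragraph.

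The cost is one sentence under Sample size calculation and a loss allowance that reads slightly less favourably. The arms, the 70 blocks of four and the recruitment target stay as they are, and no patients are added.
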